### Interim analyses {21b}

The monitoring committee will act in an advisory role to ensure safety by reviewing the cumulative data from the clinical trial at specified intervals. Its tasks also include monitoring the clinical trial’s current validity and scientific value. The monitoring committee may recommend modifying or terminating a clinical trial based on any perceived safety concerns, regardless of statistical significance. The sponsor is authorized to stop the study at any time if the safety of the participants is compromised. The test may end prematurely, especially if:Serious adverse events outweigh the previously positive balance of benefits and risks,Adverse events occur with such intensity and/or frequency that the proposed treatment regimen can no longer be continued.

The sponsor is responsible for reporting the discontinuation of the trial to the Bioethics Committee, giving the reason for discontinuing the trial, and informing in writing about the potential risk to the health of clinical trial participants or other persons.

### Methods for additional analyses (e.g., subgroup analyses) {20b}

No subgroup analysis is planned.

### Methods in analysis to handle protocol non-adherence and any statistical methods to handle missing data {20c}

Instances where the procedure is not conducted per protocol, must be documented along with the underlying reasons. The analysis will still include data regarding the study participants who did not undergo the procedure aligned with their randomized group. The CRO and the Sponsor will regularly review the Protocol Deviation Reports. Should repeated deviations from the study protocol occur, the Sponsor reserves the authority to suspend recruitment at a particular center based on their judgment and decision-making.

Multiple imputations will be employed to address these gaps when data is missing for the independent (explanatory) variables. This method estimates the missing values based on the observed data, ensuring a more complete dataset for analysis. Conversely, for the dependent (outcome) variable, cases with missing data will be removed (using listwise/case deletion). The analysis will then be conducted solely on the remaining complete cases, utilizing the observed values of the outcome variable. This approach aims to maintain the integrity of the analysis while accounting for missing data in a systematic manner.

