## Introduction

### Background and rationale {6a}

Atrial fibrillation (AF) is considered the most significant risk factor for stroke. A patient registry conducted across 47 countries revealed that approximately 4% of patients experienced a stroke within 1 year of being diagnosed with AF, and approximately 11% died [1]. Therefore, patients who obtain a score of ≥ 2 points on the CHA2DS2-VASc scale are classified as having Class I indications for stroke prophylaxis by the European Society of Cardiology (ESC). While oral anticoagulants remain the cornerstone of treatment, some patients may have contraindications to these medications. In such cases, transcatheter left atrial appendage closure (LAAC) serves as an alternative method for stroke prevention.

The effectiveness and safety of LAAC procedures have been established through extensive research involving randomized and observational trials [2–4]. Furthermore, it has been demonstrated that LAAC provides superior survival benefits compared to warfarin therapy [5]. However, it is important to acknowledge that the LAAC procedure carries certain risks, such as periprocedural stroke and microembolization of cerebral blood vessels, leading to SBI. The risk of periprocedural stroke is reported to be 0.17% [6]. Thus far, only limited data regarding the prevalence of LAAC-related SBI have been published. The incidence of SBI in these studies ranged from 4.8 to 52% [7–10]. Prospective and observational studies have provided evidence linking cognitive decline and the development of dementia to SBI [11]. A meta-analysis of 31 studies estimated the overall risk of dementia in AF patients with SBI at 1.48 [12].

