### Sample size {14}

Based on the assumptions that cerebral protection during LAAC would result in a favorable response in 85% of patients and that the absence of new SBI on DW MRI in the control group would affect 70% of patients, the minimum group size was estimated to be 118 individuals per group. This estimation ensured 80% power to detect the anticipated difference at a significance level of 5%. Considering a withdrawal or invalidation ratio of 2%, a total of 120 individuals will be enrolled in each group, resulting in a sample size of 240 patients for the study. This sample size is necessary to provide sufficient statistical power and enable meaningful comparisons between the study and control groups.

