## Statistical methods

### Statistical methods for primary and secondary outcomes {20a}

The primary analysis of all endpoints will be conducted using an intention-to-treat approach, wherein participants will be analyzed according to their initial randomization assignment, irrespective of the actual treatment received. Quantitative variables will be presented as either mean or median values, while qualitative variables will be reported as counts (with percentages). To assess the distribution of quantitative variables, the skewness index will be employed. Between-group comparisons will be carried out using independent *t*-tests and ANCOVA for quantitative variables. A chi-square test will be used to compare distributions between the two groups for qualitative variables.

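### Patients with a missing outcome are removed by listwise deletion, so the stated intention-to-treat analysis does not cover all randomised patients

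*Protocol article*

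**What the plan says.** **Analysis principle.** Under Statistical methods for primary and secondary outcomes {20a}: "The primary analysis of all endpoints will be conducted using an intention-to-treat approach". The same sentence defines the term: "participants will be analyzed according to their initial randomization assignment, irrespective of the actual treatment received". The tests named there are t-tests, ANCOVA and chi-square.

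**Non-adherence.** The section on non-adherence and missing data {20c} keeps non-adherent patients: "The analysis will still include data regarding the study participants who did not undergo the procedure aligned with their randomized group".

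**Missing data.** The same section treats covariates and outcomes differently. For covariates, "Multiple imputations will be employed to address these gaps when data is missing for the independent (explanatory) variables". For outcomes, "for the dependent (outcome) variable, cases with missing data will be removed (using listwise/case deletion"; and then "The analysis will then be conducted solely on the remaining complete cases".

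**Expected loss and follow-up.** Sample size {14} allows 2% for withdrawal or invalid data. The abstract gives 2 years of observation. Plans to promote participant retention {18b} foresees patients who cannot attend for health or other reasons, and plans telephone contact and remote interviews.

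**Visits.** In Table 1, post-procedure DW MRI is at Visits 2 and 5. After the procedure, MoCA and TMT are at Visits 2 to 5, COWAT at Visits 2, 4 and 5, and HADS at Visits 4 and 5. All four scores are also taken at Visit 1, before the intervention.

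The article gives no rule for death before an assessment and no sensitivity analysis for missing outcomes.

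**The concern.** The deletion rule is a positive statement, not a gap left to an analysis plan. A later plan could add sensitivity analyses, but the primary handling is already fixed.

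Deleting patients whose outcome is missing gives an unbiased treatment comparison only if, given arm and any covariates in the model, being observed is unrelated to the outcome. The article neither states nor defends that condition, and the endpoints make it doubtful. Cognitive decline, dementia and depression can each keep a patient from a test visit, and serious illness can prevent a scan. A remote interview may tell the investigator how the patient is, but it cannot supply a DW MRI.

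The exposure is greatest at the end of the 2 years, where the cognitive and mood hypotheses are tested. It extends to the primary endpoint if the Visit 5 scan counts; Outcomes {12} does not say which scan defines it.

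The rule also puts effort in the less important place. Missing covariates are imputed, while missing outcomes, where most of the risk of bias lies, are dropped. A completer t-test or ANCOVA at one visit makes no use of the same patient's scores at other visits.

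**Working it through.** **Inputs.** From Sample size {14}: 85% favourable response with the device, 70% of controls without a new SBI, 80% power, 5% significance (taken as two-sided), 118 per group, 120 after the 2% allowance. All missingness patterns below are assumptions. The primary endpoint is a number of foci, but the only effect size in the document is the lesion-free proportion, so the check uses that scale.

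**1. The plan's own figure.** Unpooled normal approximation:

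n = (1.960 + 0.842)² × (0.70×0.30 + 0.85×0.15) / 0.15² = 7.849 × 0.3375 / 0.0225 = 117.7, so 118 per group. This matches. For the allowance, 118/0.98 = 120.4, against 120 stated; the difference is trivial.

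**2. Power lost by deletion alone** (same formula, 120 per arm before loss):

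| Loss | Analysed per arm | Power |
|---|---|---|
| 0% | 120 | 80.7% |
| 2% | 117.6 | 80.0% |
| 5% | 114 | 78.7% |
| 10% | 108 | 76.5% |

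Power is not the main issue.

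**3. Same mechanism in both arms.** Let a lesion-free patient be missing with probability a and a lesion patient with probability k×a. For control-arm loss L, a = L/(0.70 + 0.30k). The observed lesion-free proportion for true proportion p is p(1−a) / [p(1−a) + (1−p)(1−ka)].

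For L = 2% and k = 5: a = 0.02/2.2 = 0.00909. Control 0.6936/0.9800 = 70.8%; device 0.8423/0.9855 = 85.5%; difference 14.7 points.

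| Control-arm loss | k = 2 | k = 5 |
|---|---|---|
| 2% | 14.9 | 14.7 |
| 5% | 14.7 | 14.2 |
| 10% | 14.3 | 13.3 |

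The true value is 15.0, so this pattern attenuates the effect.

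**4. Worst- and best-case bounds.** Observe 70% and 85% among scanned patients, with fraction m missing per arm. Assigning all missing patients against, then in favour of, the device gives 15.0(1−m) ± 100m points.

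- 2 of 120 missing per arm (m = 0.0167): 14.75 ± 1.67, so 13.1 to 16.4 points.
- 12 of 120 missing per arm (m = 0.10): 13.5 ± 10.0, so 3.5 to 23.5 points.

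**5. Extreme one-sided pattern.** Suppose no true effect (70% lesion-free in both arms), and that only device-arm lesion patients go missing, at fraction q. The spurious benefit is 0.70/(1−q) − 0.70. The chance of a significant false benefit is 1 − Φ[(1.96×SE₀ − benefit)/SE₁], with SE₀ the pooled and SE₁ the unpooled standard error.

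| q | Spurious benefit | Chance of false benefit (nominal 2.5%) |
|---|---|---|
| 2% | 1.4 points | about 4% |
| 5% | 3.7 points | about 9% |
| 10% | 7.8 points | about 26% |

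Steps 3 and 5 show that the bias can run either way, depending on whether the mechanism differs by arm.

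**6. Cognitive and mood scores.** The article gives no effect size, variance or power for these, so no comparable figure can be computed. The point there rests on the visit schedule and on the link between the outcome and attendance.

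**The case against.** **Intention-to-treat on the document's own terms.** A reader might infer that the two sections contradict each other. They do not, strictly. Section {20a} defines the term by randomised arm versus treatment received, and {20c} respects that by keeping non-adherent patients. Complete cases can still be compared by randomised arm. What stands is narrower: the analysis leaves out randomised patients, which falls short of the full-set meaning most readers attach to the term.

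**Who is deleted.** A reader might infer that the deleted patients are those who had a stroke, died or declined. No section says which patients will lack outcomes. Section {18b} mentions health-related reasons alongside others, and plans active follow-up. Informative missingness is plausible, not established.

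**The early scan.** The background section {6a} puts periprocedural stroke at 0.17%, or 0.0017 × 240 = 0.4 patients. Silent infarcts give a patient no symptom that would prevent a scan, and Visit 2 is the first visit after the intervention. Overt stroke is therefore unlikely to remove many patients from the Visit 2 scan. This stands, and it is why the primary-endpoint effect is small at low loss.

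**Earlier visits.** A reader might infer that a patient who misses the last visit loses all earlier scores. The text removes cases missing the outcome being analysed. If each visit is tested separately, an earlier score stays in its own comparison. The fair criticism is that it contributes nothing to the comparison at the missed visit.

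**Mortality.** It is tempting to carry forward the registry statement that "approximately 11% died" and charge the loss to the deletion rule. That figure concerns the first year after AF diagnosis in another population, and no method restores a score after death.

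**Imputing covariates.** This is not pointless, since ANCOVA is planned. Tipping-point analyses do commonly sit in an analysis plan. Neither point changes the fixed primary rule.

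**Conclusion.** The point holds in limited form. Complete-case analysis is fixed as the primary handling of every outcome, not all randomised patients are analysed, and the assumption that would justify this is not stated.

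For the primary endpoint the consequence is small if loss stays at the planned 2%: about 14.7 to 14.9 points instead of 15.0 under a shared mechanism. It becomes material if loss approaches 10%, where the data alone would leave the difference anywhere from about 3.5 to 23.5 points. These figures assume the planning proportions of 70% and 85%, and the bounds assume equal loss per arm. The 10% is an assumption, not a forecast.

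The stronger case for change lies with the 2-year cognitive and mood outcomes and any late DW MRI, where the condition being measured can itself cause the missed visit. The size of bias there cannot be derived from the document.

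**What to change.** Amend section {20c} before unblinding, and align {20a} with it.

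- **Status of complete cases.** Keep complete-case analysis as a sensitivity analysis only.
- **MoCA, TMT, COWAT and HADS.** Use a baseline-adjusted mixed model for repeated measures with all collected visits, and report deaths by arm alongside. HADS has only two post-procedure visits, so the gain there is smaller.
- **DW MRI.** Count an overt stroke or stroke death before the scan as a new lesion, or give it the worst rank if the number of foci is analysed. Multiply impute other missing scans by arm from baseline and any available post-procedure data, and add a tipping-point check. A patient who misses Visit 2 altogether will also lack that visit's NIHSS and cognitive scores, so the imputation model must not depend on them.

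The cost is protocol wording and some programming; no new data or patients are needed. The downside is that the mixed model and the imputation rest on assumptions of their own, namely that missingness depends only on observed data. These must be stated, and for the scans the tipping-point check is there to test them.

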### Plans to give access to the full protocol, participant-level data and statistical code {31c}

The protocol may be made available by the principal investigator upon reasonable request.

## Oversight and monitoring

### Composition of the coordinating center and trial steering committee {5d}

The study's sponsor is the Silesian Centre for Diseases in Zabrze, which also serves as the coordinating center for the study. Managing the Clinical Research Organization tasks has been delegated to an external organization named BioStat sp z o.o. The Silesian Centre for Heart Diseases in Zabrze is responsible for establishing contracts with other participating centers and providing the necessary equipment and materials for conducting the study.

Furthermore, a Steering Committee has been instituted to oversee the clinical trial’s scientific and operational aspects. This committee convenes regularly to supervise participant recruitment, overall data collection, and any instances of site-specific non-compliance with the study protocol. It also evaluates and follows up on recommendations by the monitoring committee, addresses operational concerns that might arise warranting modifications to the study protocol or corrective actions, and establishes a policy for publishing findings from the clinical trial’s collected data.

### Composition of the data monitoring committee, its role and reporting structure {21a}

Team of Data Managers BioStat Sp. z o. o. is responsible for data management and monitoring. The eCRF.bizTM system has many tools to monitor the progress and status of the study in real-time. In addition, the clinical database of the LAAC-SBI study has been equipped with validators and transition rules. To ensure adequate data quality control, the Data Managers team of BioStat Sp. z o. o. will apply additional data verification procedures on the database snapshot exported from eCRF.bizTM to personal computers. To increase the accuracy and repeatability of verification, Data Managers will develop a series of scripts in the R statistical program and use MS Excel. The quality control of the clinical database dumps will take place at the beginning of the study after the inclusion of each subsequent ten patients (however, at intervals not longer than 1 month). Once all patients are included, the verification frequency will increase to at least one check per week.

### Adverse event reporting and harms {22}

Any Adverse Events (AEs) or Adverse Device Events (ADEs) that meet the criteria for severity must be promptly reported to the Sponsor within 24 h of their occurrence or as soon as awareness of their occurrence is established. The same procedure applies to instances of Product Defects that could potentially lead to Serious Adverse Events (SAEs) if appropriate action had not been taken, interventions were not carried out, or circumstances were less favorable.

On an annual basis throughout the study duration, the Principal Investigator will furnish the Ethics Committee that issued the study’s approval with a comprehensive list encompassing all suspected serious adverse events that transpired within that specific year. Furthermore, an annual report about patient safety will also be submitted. Information related to all SAEs will be incorporated into the finalized Clinical Study Report.

### Frequency and plans for auditing trial conduct {23}

The Clinical Research Associate (CRA) employed by BioStat Sp. z o. o. is tasked with overseeing the following study-related visits:Initiation Visit: This visit occurs prior to center activation to verify its readiness to initiate the study. The monitor assesses facility equipment, explains relevant regulations and protocol requirements, and conducts any necessary staff training.Monitoring visits: These visits are conducted to protect study participants’ rights, adherence to the protocol and applicable regulations (including Good Clinical Practice), accurate collection and reporting of safety data, and study endpoints.Closing Visit: The closing visit is conducted to ascertain the completeness of study data and documentation, confirming that all required audit-related procedures have been executed.

The frequency of monitoring visits to each center is contingent on the pace of patient recruitment and the quality of work. The study accommodates up to 64 monitoring visits. Around 60 patients will be included in the Source Data Verification pool, enabling the verification of approximately 25% of the data. Following each monitoring visit, the CRA will compile a visit report and send a summary letter detailing the visit’s outcomes to the center.

### Plans for communicating important protocol amendments to relevant parties (e.g. trial participants, ethical committees) {25}

To ensure the flow of all relevant and up-to-date information regarding the audit on an ongoing basis, the implementation of updated documents describing the procedures, compliance with deadlines, and conducting training, detailed requirements regarding the method and frequency of communication were set out in the Project Management Plan. The first contact person for the Sponsor is the Project Manager (PM) at Biostat Sp Z o.o. The PM also acts as the initial point of contact for the monitoring team. In turn, the PM provides the Sponsor and the monitoring team with all information requiring their attention on an ongoing basis. In urgent situations, especially those concerning safety in the study, the monitoring team/Sponsor will also send their notification by e-mail to the PM and the entire team.

The first point of contact for the center is the CRA. The CRA should contact the center to conduct necessary training and discuss current topics such as available study updates, deadlines, recruitment, eCRF completion and response to data input queries, center supplies, and other open issues. Any protocol amendments will be reported to the Ethics Committee and registered to ClinicalTrials.gov.

### Dissemination plans {31a}

The study results will be announced through peer-reviewed publications and conference reports.

## Discussion

LAAC procedures have emerged as a minimally invasive alternative for stroke prevention in patients with non-valvular AF, offering an alternative to long-term anticoagulant use and its associated bleeding risks. Randomized trials have demonstrated that LAAC is non-inferior to warfarin or new oral anticoagulants in terms of efficacy for stroke prevention. However, these procedures are not without risks, particularly during the peri-procedural period. While life-threatening complications such as stroke, cardiac tamponade, and device embolization have been reported, the incidence of SBI and their potential impact on cognitive and mood disorders have not been extensively studied in large trials. It is crucial to fully understand the potential harms associated with LAAC procedures to guide appropriate pharmacotherapy and the use of neuroprotection devices.

Moreover, the issue of SBI and the need for neuroprotection devices extends beyond LAAC and can be relevant to other endocardial procedures like AF ablation or percutaneous mitral valve procedures. The presence of a thrombus in LAA is a contraindication for these procedures. However, in clinical practice, the situation can be more complex, as small micro embolic foci may arise from damaged tissue during embolization of the cerebral circulation. Additionally, decreased left atrial flows can result in echocardiographic findings of self-contrasting blood or sludge, indicating a higher risk of SBI. Therefore, considering the application of mechanical neuroprotection to a broader patient population undergoing these procedures may be reasonable. Importantly, data from the literature suggest that neuroprotection devices offer high safety in routine clinical practice.

In summary, while LAAC procedures have demonstrated efficacy in stroke prevention, the potential risks, including SBI and its impact on cognitive and mood disorders, must be thoroughly evaluated. The potential beneficial effect of cerebral protection devices in reducing the risk of SBI and the subsequent cognitive impairment and mood disorders associated with LAAC procedures would have significant implications for clinical management standards. The findings of this study can potentially shape guidelines and recommendations for the use of cerebral protection devices during LAAC and other left atrial interventions, such as AF ablation. If the study demonstrates a favorable outcome with reduced SBI incidence and improved cognitive and mood outcomes in patients receiving cerebral protection devices during LAAC, it suggests that similar benefits could be extrapolated to other left atrial interventions. This would support the use of neuroprotection devices in procedures like AF ablation, where the risk of embolic events and subsequent brain injury may also be present. However, it is important to await the current study’s results to evaluate the impact and benefits of cerebral protection devices on SBI and related outcomes in patients undergoing LAAC.

